## Abstract

**Purpose:**

HLA sensitization significantly limits donor availability and increases waitlist mortality in pediatric heart transplantation (HT). Current desensitization strategies are largely ineffective or equivocal. Recent adult studies show that a dual approach with Carfilzomib (CFZ), a proteasome inhibitor, and Belatacept (BELA), a costimulation blocker, reduces class I and II HLA antibodies (Abs). This study will evaluate the clinical utility of CFZ and BELA in reducing HLA antibody type and strength in pediatric and young adult patients.

**Methods:**

This prospective, observational study will include about 30 patients from 6 pediatric clinical sites, an HLA core and a mechanistic core lab. Patients aged 10–24 years, highly sensitized with class I and/or class II cPRA ≥ 50% (MFI > 4000), will be included. Exclusion criteria: EBV seronegative, HIV+, and a history of hematologic malignancy. Secondary endpoints include mechanistic studies on how desensitization affects cellular subsets producing HLA Abs, whether reductions in antibody strength persist until transplant, and post-transplant outcomes such as antibody mediated rejection and graft survival.

**Results:**

The study’s unique design harmonizes the use of a novel protocol across sites using a central IRB and is the first prospective, registry-based investigation in pediatric HT using the Pediatric Heart Transplant Society (PHTS) registry. The HLA core will measure antibody response through MFIs, titers, and cPRA, while the mechanistic core will use advanced investigations to support the trial's clinical endpoints.

**Conclusion:**

This multicenter study aims to establish a transformative, standardized approach to desensitization and antibody evaluation.

## Introduction

The presence of antibodies (Ab) targeting non-self human leukocyte antigens (HLA), also known as HLA sensitization, is a major barrier to heart transplantation (HT) in pediatric and young adult patients, increasing both wait times and waitlist mortality^1^. Attesting to the gravity of this problem, an analysis of all children listed for isolated HT from 1995 to 2009 in the USA found that requiring a negative prospective crossmatch (-XM) increased waiting time and more importantly increased waitlist mortality^2^. The Clinical Trials in Organ Transplantation in Children (CTOTC-04) study observed that PHT across a +XM, in sensitized patients (MFI > 1000) was associated with acceptable first year graft and patient survival, although AMR rates were high and correlated with higher DSA strength^3^. A recent analysis of the PHTS Registry found that of the 4599 pediatric heart transplants (PHT) performed between 2010–2021, 9.5% of transplants were performed across a +XM. No significant difference was noted in 10-year survival between the +XM vs. -XM groups, however, a cPRA > 50% in the +XM group emerged as a significant risk factor for graft loss^4^. A recent analysis of the United Network for Organ Sharing (UNOS) database found that both 1-year mortality (nearly 30%, a 4-fold increase) and graft loss were higher in highly sensitized (cPRA > 80%) pediatric patients compared to non-sensitized patients, and +XM was also associated with increased risk of mortality and graft loss^5^. Collectively, sensitization reduces access to transplant by limiting the donor pool and +XM in patients who are highly sensitized (cPRA > 50%) shortens post-transplant graft survival defining an unmet need.

Despite these consequences, there is no standard-of-care approach to the sensitized PHT candidate. Importantly, desensitization is used less commonly than in the adult population, with only 25% of the patients in the above cohort receiving desensitization treatment. The implications of anti-HLA Abs on transplantation vary based on antibody strength as defined by mean fluorescence intensity (MFI) and antibody titer^6^. The presence of HLA Ab is determined by the Luminex single antigen bead (SAB) assay; we will define MFI in titer as a surrogate for antibody strength. Access to the donor pool is determined by entering unacceptable antigens based on center specific MFI cut off values into the online UNOS (United Network for Organ Sharing) calculator to determine the calculated panel-reactive antibodies (cPRA). The percent cPRA informs the clinical team as to the degree of sensitization, with a higher cPRA further limiting the donor pool (Figure 1). For example, a cPRA_MFI>4000_≥ 50% indicates that >50% of donors would be unacceptable because they have HLA antigens to which the HT candidate has HLA antibodies at levels > 4000 MFI**.** The change in cPRA on neat (undiluted) serum is an insensitive measure of effectiveness, and instead, the circulating HLA Ab should be risk stratified by performing serial dilutions with cPRA reduction calculated per antibody titer^7^, ^8^. This approach allows the clinical team to differentiate between HLA antigens that should be avoided from those that are potentially acceptable to cross. Dilutional analysis can act as a surrogate for complement-binding capacity (e.g., C1q positivity), and reduction in cPRA at lower titer thresholds has been associated with improved transplant outcomes.

**Figure 1 fig0005:**
[figure not shown]
Conceptual schema for a sensitized patient. Desensitization therapy is considered for patients with strongly binding anti-HLA antibodies and a calculated panel-reactive antibody (cPRA) of greater than 50%.

For highly sensitized candidates, various desensitization strategies can be employed in an effort to eliminate or decrease the strength of anti-HLA Ab, thereby decreasing the cPRA, increasing the donor pool, and maximizing the likelihood of transplantation. Efficacy of desensitization can be assessed based on percent of antibodies that drop to low titer (<1:16) post-treatment^9^. Desensitization strategies, however, are used rarely and have unclear efficacy^10^, ^11^, ^12^, ^13^, ^14^. Distinct from adult transplant candidates, pediatric candidates are i) more likely to have congenital heart disease, where exposure to bypass and homograft during prior palliative procedures markedly increases the risk of sensitization, and ii) less likely to benefit from long-term durable support, together underscoring the urgent need to define pathways to transplant for these patients. No standardized management protocols for desensitization in pediatric HT (PHT) exist to date.

## Desensitization strategies

Multiple strategies have been used to treat sensitization in HT candidates, mainly adapted from the renal transplant experience (Table 1). These therapies focus on multiple targets of the humoral immune pathway to either achieve a -XM pretransplant or to reduce the impact of DSA in +XM transplant. At low titer, antibody reduction can be achieved by removal with plasmapheresis and or inactivation with use of intravenous immunoglobulin (IVIG). The use of B cell depleting agents (rituximab), inhibitors of complement activation (eculizumab), inhibitors of IL-6 (tocilizumab) and monoclonal antibody against CD38 (daratumumab) remain more experimental and limited to highly sensitized patients. The current literature in adults is not abundant, mostly observational, with small cohorts, short follow-up, and with inconsistent treatment methodologies. Current pediatric literature is even more limited and efficacy of desensitization therapies in pediatric HT recipients as of yet remains unclear. While there are some studies reporting success in facilitating HT, many pediatric patients do not respond, or experience Ab rebound, highlighting the diversity of the individual patients’ immune response^10^, ^11^, ^12^, ^13^, ^14^, ^15^. Hence, there is an urgent need to standardize management protocols across centers so as to i) advance our knowledge thereby ii) informing treatment decisions for this high-risk group of patients.

**Table 1 tbl0005:** Current Strategies for Desensitization of Pediatric Heart Transplant Candidates

Drug/MOA	Summary	Limitations/Concerns
**IVIG**		
Derived from the gammaglobulin fraction of pooled human plasma. Has multiple immunomodulatory effects: neutralizes circulating antibody, inhibits complement and inhibits B cell activation and maturation through upregulation of inhibitory B-cell FcγRIIB.	Most commonly used desensitization therapy in pediatric heart transplantation, included in upto 79% of protocols. Small studies show it can reduce PRA and enable transplantation, particularly when used in combination with plasmapheresis.	Effectiveness is variable – especially when assessed with sensitive assays like single antigen bead, and cPRA reduction is often modest. IVIG is generally more effective as part of a multimodal approach rather than monotherapy.
**Plasmapheresis**		
Removes circulating immunoglobulins via extracorporeal plasma antibody filtration.	Often used alongside IVIG, has been shown to reduce PRA in some heart transplant candidates through outcomes vary by antibody burden and patient factors.	Antibody rebound due to rapid diffusion from extravascular space can occur and multiple treatments are usually needed to achieve low circulating antibody levels.
**ANTI CD20**		
**Rituximab**		
A chimeric murine/human monoclonal IgG1 antibody directed against CD20, expressed on mature B cells. Near complete depletion of peripheral blood B cells is achieved through a combination of antibody dependent cellular cytotoxicity (ADCC), complement-dependent cytotoxicity, and apoptosis.	Studies in both pediatric^16^ and adult heart transplant patients have noted cautiously optimistic results, especially when Rituximab was combined with IVIG. However, the non-randomized clinical experience has usually been heterogenous and particularly in the renal RCTs has been inadequate.	Limited ability to adequately suppress HLA Ab responses since: 1. It does not prevent denovo DSA. 2. CD20 Ag is absent on B cell precursors and antibody secreting plasmablasts/ plasma cells. 3. It incompletely eliminates CD27+ memory B cells
**PLASMA CELL INHIBITORS**		
**Bortezomib**	(described in detail in manuscript)	
**Carfilzomib**		
**Daratumumab**		
A high affinity human IgGκ monoclonal antibody that targets CD38 and induces PC apoptosis via Fcγ receptor mediated cross-linking and macrophage mediated phagocytosis. It also promotes expansion of memory and naïve T-cells^17^.	Its success in treating myeloma and AL amyloidosis has led to its off-label use in transplant settings for desensitization and AMR. CD38 is also expressed on natural killer (NK) cells, which may provide additional benefit, particularly in the setting of AMR and chronic rejection. Early case series and small trials predominantly in kidney transplantation suggest it can significantly reduce DSAs and stabilize or reverse AMR^13^. In pediatric patients, experience with daratumumab is even more limited, with only isolated case reports^18^^,36,37^ and small series that suggest potential efficacy with a decline in cPRA.	1. The efficacy may be limited by the persistence of long-lived plasma cells within bone marrow niches that can continue producing alloantibodies despite treatment. 2. Immune reconstitution could lead to the rebound effect described in the case series. 3. Since CD38 is also expressed on multiple suppressor cell lineages, there is a possibility of T cell mediated rejection following Daratumumab.
**COSTIMULATORY BLOCKADE**		
**Belatacept**	(described in detail in manuscript)	
**ANTI-IL6/IL6R**		
**Tocilizumab**		
Anti-IL6 receptor.		
Broad effects on B cell maturation, T cell activation and germinal center responses.	Have shown modest antibody reductions in highly sensitized kidney transplant candidates, especially when combined with IVIG. Outcomes vary, particularly in patients with high-titer DSA.	Limited effect as monotherapy since they are not robust inhibitors or depleting agents, thus unable to significantly alter the immune response.
**Clazakizumab**		
Direct IL6 blocker		
**COMPLEMENT INHIBITORS**		
**Eculizumab**		
Humanized anti-CD5 monoclonal antibody. Inhibition of C5 cleavage to C5a and C5b prevents the formation of C5b-9 macrophage activating complex (MAC) and its downstream effects.	Approved for the treatment of paroxysmal nocturnal hemoglobinuria and atypical hemolytic uremic syndrome, and has been used in transplantation to treat refractory antibody mediated rejection. Patel et al led a prospective trial of terminal complement inhibition after high immunologic risk heart transplantation and found that it was well tolerated with favorable post transplant outcomes. When compared with patients treated with plasmapheresis and IVIG, eculizumab was associated with dramatic decrease in incidence of biopsy proven AMR.	

## Carfilzomib and belatacept

Desensitization therapies as discussed above, generally deplete or modulate antibodies or affect B-cell activity without affecting antibody production by plasma cells. Proteosome inhibitors (PIs) induce apoptosis in response to the accumulation of misfolded proteins. The high rate of immunoglobulin synthesis by antibody secreting cells (ASCs) underlies their susceptibility to PI-based therapies. Carfilzomib (CFZ) is a 2nd generation, irreversible inhibitor of 20S proteasomal subunit. CFZ causes less neuropathy than its first-generation cousin bortezomib and may have less antibody rebound due to its irreversible binding^11^. CFZ as desensitization monotherapy in renal transplant patients led to a reduction in HLA antibodies and in bone marrow plasma cells (BMPCs) with acceptable drug safety and toxicity^16^. In HT candidates, desensitization with CFZ, plasmapheresis and IVIG led to a decrease in cPRA from 76% to 40%. A rejection episode was documented in a patient with C1q-PRA of 54% suggesting a limitation in more highly sensitized candidates^15^. From a mechanistic standpoint, bone marrow CD138+ plasma cells (PCs) secrete antibodies with specificities that mirror those in peripheral blood – underscoring their contribution to HLA sensitization. CFZ reduces CD138+ BMPCs by ≥ 50%, including the HLA repertoire in sensitized patients^17^. However, the *response is incomplete* and accompanied by brisk rebound following treatment completion^16^. While several factors are thought to contribute, homeostatic proliferation in germinal centers (GCs) is thought to drive repopulation^18^, highlighting the contribution of memory B cells, which can enter the GC leading to robust recall responses. These observations argue for combinatorial therapies targeting not only the PC compartment but also GCs and memory B cells.

The T-dependent nature of the anti-HLA antibody response suggests T-cell/B-cell interactions as a rational therapeutic target. The critical interactions include CD28:CD80/86, CD40:CD40L, and ICOS:ICOSL; and the ability to block these is collectively termed costimulation blockade^19^. The major clinical target to date has been the CD28:CD80/86 pathway and this has been achieved using the fusion protein CTLA4-Ig (abatacept) and its high affinity variant belatacept^20^. Belatacept (BELA) is a humanized IgG1 antibody against CD80/CD86 fused with CTLA4 that outcompetes T cell CD28 for interactions with CD80/86 found on antigen-presenting cells. BELA has been approved for use in renal transplant recipients on the basis of two randomized controlled trials, where compared with calcineurin inhibitor (CNI) based immunosuppression, it was associated with strikingly low incidence of *de novo* DSA and superiority in constraining pre-existing HLA Ab responses^21^, ^22^. Evidence suggests that this may be attributed to the ability of BELA to blunt germinal center (GC) responses^23^, ^24^, ^25^, ^26^. BELA has been used in adolescents and children as young as 3 years old following renal transplantation and found to be well tolerated other than some episodes of clinical neutropenia^27^.

### Study design

This is a prospective, multicenter, observational study of a dual immunotherapy approach for desensitization that will combine an intensive PI, CFZ based regimen with costimulatory blockade with BELA. This strategy is novel in PHT patients and we hypothesize that it will substantially enhance our ability to transplant highly sensitized (cPRA_MFI>4000_ ≥ 50%) pediatric/ young adult patients.

#### Primary aim

Study the efficacy and effectiveness of our proposed combined protocol with CFZ and BELA. We will investigate whether each cycle of desensitization is effective at.

i) reducing antibody strength as measured by MFI and titers and.

ii) lowering the calculated panel reactive antibody (cPRA).

We hypothesize that this protocol will lead to a meaningful decrease in antibody strength, with stepwise dilution of serum demonstrating gradual elimination or decrease in MFI such that the corresponding antigens would no longer be considered unacceptable. This would lower the cPRA, thereby allowing the use of a greater donor population. We will also determine whether the reduction in antibody strength is maintained with BELA between the last cycle and time of transplant. Reduction in DSA at the time of crossmatch will be studied to establish the functional relevance of our strategy. Sensitizing events defined per CTOT criteria^3^, as well as clinical events associated with the use of the proposed protocol will be monitored.

#### Secondary aim 1

Determine how desensitization impacts cellular subsets responsible for circulating anti-HLA antibodies. Using a series of state-of-the art techniques, we will combine global approaches (multiparameter flow, transcriptomics) with studies to delineate antigen specific responses (allo and viral) together establishing how desensitization shapes the B- and T-cell compartment and determine whether the response is sustained under BELA.

#### Secondary aim 2

Assess waitlist mortality and post-transplant outcomes using the Pediatric Heart Transplant Society (PHTS) database. We hypothesize that mortality before and after transplant will be comparable to overall PHTS outcomes^5^, both with and without positive crossmatch. Crossmatch (XM) status at the time of transplant will be recorded for each patient, and patients will be followed for at least one year after transplant to assess for antibody mediated rejection (AMR), ISHLT grade acute cellular rejection ≥2R (ACR), cardiovascular mortality, or need for retransplantation. While the primary analysis will focus on the first post-transplant year to align with available PHTS data, we anticipate extending this work in the future to evaluate longer term outcomes as data maturity allows.

Additional PHTS defined outcomes including major infections within the first post-transplant year will also be analyzed, given their relevance to overall morbidity and mortality in this population. Although development of de novo donor specific antibodies (DSA) is not explicitly captured within PHTS, this represents a key mechanistic endpoint linking sensitization to AMR and mortality. If feasible, we will explore integration of site level DSA data or use donor derived cell free DNA (dd cfDNA), which is available through PHTS, as a surrogate marker of alloimmune injury.

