### Known and potential risks

Risks associated with BELA: In the BENEFIT trial, a higher incidence of posttransplant lymphoproliferative disease (PTLD) was observed in BELA treated renal transplant recipients who were naïve for prior Epstein Barr virus (EBV) infection at time of transplant^31^. As such, we will exclude patients who are EBV seronegative. There is emerging evidence of BELA associated risks of greater CMV morbidity^32^.

Risks associated with CFZ: New onset or worsening of pre-existing cardiac failure, acute renal failure and pulmonary toxicity have been reported. Adverse reactions could include anemia, diarrhea, hypertension, fatigue, thrombocytopenia, peripheral neuropathy and dyspnea.

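### Secondary aim 2 hypothesizes about post-transplant mortality from any cause but lists only cardiovascular death as the fatal outcome; all-cause death should be named

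*Protocol article*

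**What the plan says.** Under Secondary aim 2, the purpose is to "Assess waitlist mortality and post-transplant outcomes using the Pediatric Heart Transplant Society (PHTS) database". The hypothesis follows: "We hypothesize that mortality before and after transplant will be comparable to overall PHTS outcomes". Neither sentence limits mortality by cause.

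The next sentence sets the follow-up: "patients will be followed for at least one year after transplant to assess for antibody mediated rejection (AMR"), then cellular rejection of grade 2R or higher, then "cardiovascular mortality, or need for retransplantation". The primary analysis is said to focus on the first year after transplant.

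The paragraph after it states: "Additional PHTS defined outcomes including major infections within the first post-transplant year will also be analyzed", and justifies this by the bearing of infection on morbidity and mortality. The abstract's Methods name "post-transplant outcomes such as antibody mediated rejection and graft survival" among the secondary endpoints; graft survival is not defined. Under Known and potential risks, the article lists, for belatacept, lymphoproliferative disease and CMV ("There is emerging evidence of BELA associated risks of greater CMV morbidity"). For carfilzomib it lists cardiac failure, acute renal failure and pulmonary toxicity.

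**The concern.** The hypothesis and the outcome list stand in consecutive sentences and do not match. One speaks of mortality; the other names a cause-specific part of it. An article may leave endpoint detail to a fuller document, but here it does state the fatal outcome, and states one narrower than the hypothesis needs.

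Two consequences follow if the list is used as written. First, the cohort's numerator would leave out non-cardiovascular deaths, while the mortality and survival results cited in the Introduction are not described as cause-specific. That mismatch can only favour the cohort. Second, a non-cardiovascular death removes a patient from the risk of rejection and retransplantation, so that patient could appear free of every event on the list. With about 30 patients, one or two deaths change the reading. Assigning a cause of death is also open to misclassification, which an all-cause count avoids.

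**Working it through.** **The plan's own figure.** The article gives no expected mortality for its cohort. The nearest figure is in the sample size section: 80% power for a chi-square effect of W = 0.51 with 30 patients (called Aim 3). With noncentrality 30 × 0.51² = 7.80, 1 degree of freedom and two-sided alpha 0.05 (assumed, not stated), power is 79.8%. It reproduces, is not in dispute, and does not depend on which deaths are counted.

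**What each place covers.**

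| Place | Fatal outcome | Limited by cause? |
|---|---|---|
| Secondary aim 2, purpose | Waitlist mortality | No |
| Secondary aim 2, hypothesis | Mortality before and after transplant | No |
| Secondary aim 2, follow-up list | Cardiovascular mortality | Yes |
| Secondary aim 2, added outcomes | Major infections as events; infection deaths not named | Not applicable |
| Abstract, Methods | Graft survival, undefined | Unclear |

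Only the follow-up list is restricted, and it is the only explicit statement of which deaths after transplant will be assessed.

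**How many deaths could be left out.** The documents give neither the number who will be transplanted nor the split of deaths by cause, so this is a range.

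- Transplants, n: 24 to 30. The 30 is the planned cohort; 24 is an assumption.
- One-year mortality, m: the upper end is 30%, from the cited UNOS analysis, "1-year mortality (nearly 30%, a 4-fold increase"). That result is for cPRA above 80%, whereas this study enrols from 50%. The lower end is that figure divided by the 4-fold increase: 30% / 4 = 7.5%, taken as about 7% because the source says nearly 30%.
- Non-cardiovascular share of deaths, s: 20% to 60%, assumed.

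Expected deaths outside the listed outcome = n × m × s. The chance of at least one is 1 − (1 − m × s)^n.

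| n | m | s | Expected deaths | Outside the list | Chance of at least one |
|---|---|---|---|---|---|
| 24 | 7% | 20% | 1.7 | 0.3 | 29% |
| 24 | 7% | 60% | 1.7 | 1.0 | 64% |
| 24 | 30% | 20% | 7.2 | 1.4 | 77% |
| 24 | 30% | 60% | 7.2 | 4.3 | 99% |
| 30 | 7% | 20% | 2.1 | 0.4 | 34% |
| 30 | 7% | 60% | 2.1 | 1.3 | 72% |
| 30 | 30% | 20% | 9.0 | 1.8 | 84% |
| 30 | 30% | 60% | 9.0 | 5.4 | 99.7% |

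The range is 0.3 to 5.4 deaths. Its width reflects the assumptions; no single value in it is an estimate.

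**The case against.** The strongest reply is that the article never says the mortality hypothesis will be tested with cardiovascular deaths. The hypothesis is already unrestricted, and the list after it can be read as graft-related events to follow rather than a redefinition of mortality. The list is also not closed: the abstract adds graft survival, further registry-defined outcomes are promised, clinical events associated with the regimen are to be monitored, and the registry is to transmit compiled event data. Full definitions may stand in a document not shown.

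Much of this stands, and it rules out stronger readings that a reader might infer:

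- *That a cardiovascular count will be set against an all-cause benchmark, so that the regimen looks comparable by construction.* No sentence says so. It follows only if the listed outcome is the one compared.
- *That deaths go uncollected.* Nothing in the text shows this.
- *That toxicity deaths in general escape.* Under Study regimen, carfilzomib belongs to the desensitization cycles and belatacept maintenance runs up to transplant. Deaths before transplant fall under waitlist mortality, which has no limit by cause.
- *That the regimen's harms lead mainly to non-cardiovascular death.* The documents give no such split. Carfilzomib's listed risks begin with cardiac failure, and EBV-seronegative patients are excluded because of the lymphoproliferative risk.
- *That the loss is large.* The figure near 30% belongs to a more highly sensitized group, and at the low end less than one death is expected to be left out.

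What the reply does not remove is the wording. No sentence shown names all-cause death after transplant as an assessed outcome, while one names a narrower outcome directly after the broader hypothesis.

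**Conclusion.** The point holds in limited form. The listed post-transplant fatal outcome is narrower than the hypothesis it follows. Used as written, it would not allow a like-for-like test and would tilt the comparison toward comparable. It does not touch waitlist mortality, data capture or the sample size. The direction of the tilt follows from the definitions, because a subset of deaths cannot exceed the total. Its size does not follow from the documents: the 0.3 to 5.4 deaths rest on an assumed number of transplants, an assumed split by cause, and mortality figures from a cited analysis with a different sensitization threshold. Severity is minor: this is a secondary aim in a study that calls itself preliminary, and the correction is free.

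**What to change.** In Secondary aim 2, list all-cause post-transplant mortality as the outcome that answers the hypothesis. Define the abstract's graft survival as freedom from all-cause death or retransplantation at one year. Report cause of death, including cardiovascular, as a descriptive component. State that the comparison with the registry uses the same all-cause definition on both sides.

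The cost is wording only. A comparison of mortality with the registry already needs all deaths, no sample size figure changes, and cardiovascular death is still reported.
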